### Statistics

Sample size calculation was made on the hypothesis that the average morphine equivalent consumption in patients receiving local anesthetic and steroids CWI will be reduced by 50 % as compared with those in the control group. This assumption comes from (1) our retrospective experience and audits about analgesic consumption in our institution and (2) data from previous literature [27]; they both showed reduction in morphine consumption of 30–50 % in patients receiving local anesthetic wound infusion. Given this assumption, we need 50 patients per group for a power of 80 % and an α error of 5 %; given an attrition rate of 15–20 %, 120 patients are needed in each group.

We will perform an intention-to-treat analysis, and all participants will be analyzed once enrolled. We consider a “dropout” to be any patient not completing the evaluation at 3 months (for any reason).

For descriptive variables, we plan to use mean and standard deviation for normally distributed variables and average interquartile range for skewed distributions.

We will perform group comparison by using the Student’s *t* test or Mann–Whitney test for quantitative variables and Pearson’s chi-squared test for categorical variables. Inflammation, oxidative stress, and genetic background will be assessed to see whether they are biological markers that help modulate post-operative and persistent pain: the difference in inflammatory response and oxidative stress will be analyzed by means in a uni- and multi-variate regression model for repeated measures, including time, group, and their interaction. Variables will be transformed if needed to satisfy model assumptions. Post-hoc comparisons will include within-group changes over time and between-group differences at each assessment. The *P* value will be adjusted for multiple tests. Fisher exact test will be used to evaluate the impact of genetic background. The odds ratio and 95 % confidence interval will be computed with logistic regression. The *P* value to assess statistical significance will be corrected with the Bonferroni correction depending on the number of candidate genes tested.

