**Methods/Design:**

After approval by their institutional review board, three hospitals will enroll 120 patients undergoing major abdominal surgery in a randomized, double-blind, phase III study. After a 24-h CWI of ropivacaine 0.2 % + methylprednisolone 1 mg/kg, patients will be randomly assigned to receive either ropivacaine + steroid or placebo for the next 24 h. Then, patient-controlled CWI with only ropivacaine 0.2 % or placebo (according to the group of randomization) is planned after 48 h up to 7 days (bolus 10 ml, lock-out 1 h, maximum dose of 40 ml in 4 h). Morphine equivalent consumption up to 7 days will be analyzed, together with any catheter- or drug-related side effect. Persistent post-surgical pain (PPSP) incidence will also be investigated. Our primary endpoint is analgesic consumption in the first 7 days after surgery; we will evaluate, as secondary endpoints, any catheter- or drug-related side effect, genotype/phenotype correlations between some polymorphisms and postoperative outcome in terms of morphine consumption, development of the inflammatory response, and incidence of PPSP. Finally, we will collect, in a subgroup of patients, wound exudate samples by micro-dialysis, blood samples, and urine samples up to 72 h to investigate local and systemic inflammation and oxidative stress.

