### Procedures - clinical study

On the day of surgery, patients come to the operating room and are provided with standard monitoring (electrocardiogram, oxygen saturation, non-invasive blood pressure, and invasive pressure monitoring). General anesthesia is given using propofol and midazolam (as deemed appropriate by the anesthesiologist), opioids (fentanyl 0.2 μg/kg or remifentanil 0.1-0.25 mg/kg per min or both), and muscle relaxants (cisatracurium/rocuronium) and maintained with sevoflurane.

A morphine bolus of 0.15 mg/kg is given 30 to 45 min before the end of surgery. An infusion catheter (Baxter Painfusor®; Baxter International, Deerfield, IL, USA) is placed by the surgeon in the fascial plane between peritoneum and fascia trasversalis, and a 10-ml bolus of 0.2 % ropivacaine is administered immediately after muscular plane closure; the catheter is then connected to an electronic pump (CADD®-Solis; Smiths Medical, Dublin, OH, USA) to give a continuous infusion of pain medications.

During the first 24 h, all patients receive ropivacaine 0.2 % + methylprednisolone 1 mg/kg, 10 ml/h (total volume of 240 ml in 24 h) continuous wound infusion; additionally, either acetaminophen 1000 mg or ketorolac 30 mg every 8 h is prescribed.

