### Study outcomes

The primary outcome of the study is to investigate whether a wound infusion of local anesthetic and steroid has a higher analgesic efficacy compared with placebo during 7 days following surgery, assessed as analgesic consumption: the primary endpoint will be the reduction of morphine equivalents required in the first 7 days after surgery.

Secondary outcomes will include the differences in analgesia and side effects within 7 days after surgery. We will investigate any difference in pain at rest and movement (i.e., coughing and deep inspiration) by Numeric Rating Scale (11-point scale from 0 = no pain to 10 = worst imaginable pain), additional analgesic consumption, side effects (postoperative nausea and vomiting, sedation, and any signs of local anesthetic or steroid systemic toxicity), and incidence of persistent post-surgical pain. Differences in terms of wound healing or wound infections will be also assessed up to 3 months to assess any local side effect of steroid infusion. The degree of inflammatory response/oxidative stress between groups will be assessed to analyze the effect of CWI with either treatment or placebo. We plan to analyze the combined effect of some polymorphisms (by using a gene-candidate approach) of genes related to the development of PPSP, pain sensitivity, opioid response, and inflammatory reaction.

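### The 80 % power rests on a 50 % reduction that is not supported for the contrast actually randomised, and the primary objective misstates the comparator

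*Protocol article*

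**What the plan says.** Statistics gives the planning hypothesis: mean morphine-equivalent consumption in patients given local anesthetic and steroid wound infusion "will be reduced by 50 % as compared with those in the control group". Two sources are named, the institution's own retrospective experience and audits, and previous literature: "they both showed reduction in morphine consumption of 30–50 % in patients receiving local anesthetic wound infusion". From this follows "we need 50 patients per group for a power of 80 % and an α error of 5" %, and then "given an attrition rate of 15–20 %, 120 patients are needed in each group". The Abstract (Methods/Design) instead says that "three hospitals will enroll 120 patients undergoing major abdominal surgery", and the Discussion also gives 120 for the trial.

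Study outcomes states the primary objective as testing "whether a wound infusion of local anesthetic and steroid has a higher analgesic efficacy compared with placebo during 7 days following surgery", measured by morphine equivalents over the first 7 days.

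The treatment sections describe a different comparison. Under Procedures - clinical study: "During the first 24 h, all patients receive ropivacaine 0.2 % + methylprednisolone 1 mg/kg, 10 ml/h". The next section places random assignment after those 24 h. One arm continues ropivacaine plus methylprednisolone and the other changes to saline; from 48 h both move to patient-controlled wound boluses of ropivacaine alone or saline.

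**The concern.** The assumed effect and the randomised contrast do not match. The 30–50 % is described for patients receiving a local anesthetic wound infusion. Here both arms receive an active infusion on the first day, and they differ only in whether active treatment continues. The plan takes the largest reduction it cites and carries it over without arguing that continuing rather than stopping at 24 h has an effect of that size.

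Two things are at stake. First, the single figure of 80 % conveys more assurance than the plan's own evidence gives. Second, the objective's wording fixes what the trial will claim. No patient receives placebo for the 7 days after surgery, so neither a positive nor a null result answers the question as worded. A null result could mean that the first 24 h had already given much of the benefit.

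**Working it through.** **Inputs.** From Statistics: 50 per group, 80 % power, α 5 %, assumed reduction 50 %, cited range 30–50 %, attrition 15–20 %, Student's t or Mann–Whitney test. Not given: sidedness (two-sided assumed), SD and control mean. Without the last two, the 50 per group cannot be reproduced independently; it can only be solved backwards.

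**Step 1: implied SD.** Express the reduction r and the SD σ as fractions of the control mean. With n per group, power ≈ Φ(r·√(n/2)/σ − 1.96). Setting n = 50, r = 0.50 and power 80 % gives 0.50 × 5/σ = 2.802, so σ = 0.892. The t-test version gives a standardised difference of 0.566 and σ = 0.884. With this σ the plan's 80 % is recovered by construction.

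**Step 2: number per group.** 50/(1 − 0.15) = 58.8, so 59; 50/(1 − 0.20) = 62.5, so 63. This fits 120 in total, or 60 per group, and not 120 in each group. Dropout is defined by the 3-month evaluation, so the number analysed for a 7-day endpoint plausibly lies between 50 and 60 per group.

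**Step 3: power over the plan's own range, σ held at 0.892.**

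| Reduction | 50 per group | 60 per group |
|---|---|---|
| 50 % | Φ(2.802 − 1.96) = 80 % | Φ(3.069 − 1.96) = 87 % |
| 40 % | Φ(2.241 − 1.96) = 61 % | Φ(2.455 − 1.96) = 69 % |
| 30 % | Φ(1.681 − 1.96) = 39 % | Φ(1.841 − 1.96) = 45 % |

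The t-test calculation agrees to the percentage point. For 80 % power, 79 per group would be needed at 40 % and 139 at 30 %.

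**Step 4: sensitivity to the SD assumption.** If the SD is proportional to the mean in each arm (again solved to give 80 % at 50 %), power at 30 % with 50 per group is 34 %. On a log scale it is 30 %. The direction does not change.

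**Step 5: the common first day.** The 7-day total includes 24 h in which both arms are treated alike. If a share f of control consumption falls there, a 50 % difference in totals requires a reduction of 0.50/(1 − f) afterwards. The documents do not give f. As an assumption, f = 0.2 requires 0.50/0.8 = 62.5 %, which is above the cited range. The power figures in Step 3 do not use this.

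**The case against.** - **The power statement is conditional.** The plan says what is needed given the 50 % assumption, and at a 50 % difference 80 % is correct. This stands, and it rules out calling the stated power wrong.
- **The steroid could justify the upper end.** The cited range is for local anesthetic, while the trial arm adds methylprednisolone, which the Background and Discussion expect to add efficacy. It also offers wound analgesia for up to 7 days, where the Discussion says most studies used two. This is a fair reason to hope for 50 %, but Statistics does not make the argument, and on the first day the steroid cannot separate the arms because both receive it.
- **Carry-over is speculative.** One might infer that lasting benefit from the first 24 h shrinks the later difference by a known amount. The documents give no such figure, and the Background and Discussion argue that sensitization restarts once analgesia stops, which points the other way. Illustrative carry-overs of 5, 10 and 20 percentage points give 71 %, 61 % and 39 % power if the SD stays fixed, but 76 %, 70 % and 56 % if it scales with the control mean. They show sensitivity and are not evidence.
- **The literal text says 120 in each group.** If all of those were analysed, power at 30 % would be about 74 %. The Abstract, the Discussion and the attrition arithmetic all point to 120 in total.
- **The design is disclosed.** The shared 24 h is stated openly, and the Discussion defends it as no methodological bias, with a planned look at 24-h morphine consumption. That deals with imbalance between the arms. It does not address the size of the expected effect or the wording of the objective.

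**Conclusion.** The point holds in this form: a 50 % reduction, and hence 80 % power, is not supported for continuing versus stopping active wound treatment at 24 h, and the primary objective names a comparator that the trial does not randomise. Within the plan's own 30–50 %, power runs from 39 % to 80 % with 50 analysed per group and from 45 % to 87 % with 60. This assumes a two-sided 5 % test, the back-solved SD and 120 patients in total.

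A reader might go further and infer that the 80 % is false, or that the trial's power is 39 %. The documents support neither. The 80 % is right if the difference between these arms is 50 %, and the true difference, SD, control mean, first-day share and any carry-over are all unknown. The size of the power loss therefore cannot be fixed.

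**What to change.** Keep the sample size and change two passages.

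1. **Study outcomes, and the conclusion drawn from it.** State the primary objective as continuing active wound treatment after 24 h versus switching to saline, following 24 h of active infusion in all patients.
2. **Statistics.** State that 80 % power holds only for a 50 % difference between these two arms, and that 50 % is the upper end of what was seen with local anesthetic wound infusion. Give power across the cited range: about 61 % at 40 % and 39 % at 30 % with 50 analysed per group, and 69 % and 45 % with 60. If the added steroid is the reason for choosing 50 %, say so. Correct the count to 120 in total.

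The cost is wording only, with no added patients or procedures. The downside is a less favourable power statement and a narrower claim.

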In regard to local side effects, the main concerns are about wound healing and infections potentially associated with immune-modulatory action of steroids. Most of the existing data deal with high doses of systemic steroids [29, 30]. Up to now, few studies have addressed these issues in patients receiving peripheral steroids: these studies are in the orthopedic setting and investigate only clinical effects of a single-shot administration and provide no evidence of increased infections or difficult healing [29, 30]. We therefore plan to clarify the risk/benefit ratio of continuous administration of methylprednisolone, strictly monitoring wound healing and any potentially harmful effect of CWI.

We decided to treat all the patients with 24-h CWI of ropivacaine and methylprednisolone. This will enlarge the sample size for the phase III trial (120 patients) and will allow us to investigate the differences in locally released cytokines according to suspension of local anti-inflammatory treatment after the first 24 h. This, in our opinion, does not configure a methodological bias, as our primary endpoint is analgesic consumption at 7 days, and we will take care to evaluate any statistically significant difference in morphine consumption at 24 h to eliminate any confounding factor this kind of study design may potentially imply.

Furthermore, an ethical issue arises: because CWI with local anesthetics is already documented as a valuable analgesic strategy [8], switching to a saline infusion after 24 h in the control group may be questioned. Otherwise, placebo control is still a key feature for high-quality clinical trials in the perspective of determining the actual effectiveness of treatments. Furthermore, because we are investigating local inflammation, comparing analgesic efficacy with cytokine analysis will help clarify whether the pain-killing effect of CWI is associated either with methylprednisolone’s action or with a “washout” phenomenon (i.e., on the steroid’s effect on cytokine release rather than on cytokine dilution by fluid infusion).

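### The Statistics section asks for 120 patients in each group, about twice the roughly 60 per group that its own inputs give; the 120 in total planned elsewhere fits those inputs

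*Protocol article*

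**What the plan says.** The sample-size paragraph in the Statistics section of the protocol article assumes that mean morphine-equivalent consumption "will be reduced by 50 % as compared with those in the control group". On that basis it states that "we need 50 patients per group", for 80 % power and a 5 % α. It then allows for attrition of 15 to 20 % and concludes that "120 patients are needed in each group".

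Two other places give the size of the trial. The Abstract (Methods/Design) says that "three hospitals will enroll 120 patients undergoing major abdominal surgery". The Discussion, in explaining why every patient receives the active infusion for the first 24 hours, says: "This will enlarge the sample size for the phase III trial (120 patients", closing the bracket there. Both refer to the trial as a whole. The Methods describe two randomized groups, so the Statistics sentence amounts to 240 patients. The figure 240 appears nowhere in the article.

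**The concern.** The conclusion of the sample-size paragraph does not follow from the two numbers just before it, and it conflicts with the enrolment figure in the Abstract and the Discussion. An allowance of 15 to 20 % cannot turn 50 into 120.

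This matters because the Statistics section is the only place where the recruitment target is derived, and it is where a monitor, ethics committee or later reader will look for the planned size. Taken literally, it calls for 120 patients more than the Abstract does. A trial that closed at 120 could then be read as having recruited half its requirement. The Trial status section reports 46 patients enrolled and recruitment still open, so the stopping number had not been reached under either reading.

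**Working it through.** **Inputs from the Statistics section**
- Patients needed per group before attrition: n = 50.
- Attrition: d = 15 to 20 %.
- Stated result: 120 per group.

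**Inputs from elsewhere**
- Two randomized groups (Methods). Equal allocation is assumed, because one per-group number is given for both.
- Enrolment of 120 for the trial (Abstract; Discussion).

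**Step 1. Try to reproduce 120 per group.**

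Usual inflation, n/(1 − d), rounded up:
- d = 15 %: 50/0.85 = 58.8, so 59 per group, 118 in total.
- d = 20 %: 50/0.80 = 62.5, so 63 per group, 126 in total.

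Cruder inflation, n × (1 + d), rounded up:
- d = 15 %: 50 × 1.15 = 57.5, so 58 per group, 116 in total.
- d = 20 %: 50 × 1.20 = 60 per group, 120 in total.

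Neither rule comes near 120 per group anywhere in the stated range.

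**Step 2. What attrition would 120 per group imply?**

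1 − 50/120 = 58.3 %, almost three times the upper end of the stated range (58.3/20 = 2.9).

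**Step 3. Does 120 in total fit?**

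120/2 = 60 per group, and 1 − 50/60 = 16.7 %, which lies inside 15 to 20 %. Under the cruder rule, 60 per group is exactly the result at 20 %. The figure of 120 therefore follows from the paragraph's inputs as a total but not as a per-group number.

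**Step 4. What does 60 per group leave after attrition?**
- 15 %: 60 × 0.85 = 51 per group.
- 16.7 %: 60 × (50/60) = 50 per group.
- 20 %: 60 × 0.80 = 48 per group, two short of 50.

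**Limit of the check.** The 50 per group cannot be re-derived, because the article gives no control mean, standard deviation, sidedness or test for the calculation. Steps 1 to 4 take the 50 as given and do not depend on how it was obtained.

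**The case against.** The strongest reply is that this is a slip of wording. The Abstract states the enrolment plainly, the Discussion repeats it, 240 is never mentioned, and 120 in total is what the inputs support. Most readers would conclude that the words after the number should have said in total. That is probably right, and it limits the point to the one phrase. It does not remove the point: the sentence as printed is wrong, and nothing else in the article corrects it.

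Three stronger readings are tempting, and the document does not support them.

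- A reader might infer that the trial's recruitment target is itself wrong by a factor of two. Only the per-group figure in the Statistics section is. The target in the Abstract and the Discussion agrees with the inputs.
- A reader might infer that 120 in total misses the planned 80 % power, at about 78 % with 48 evaluable per group. That figure requires an effect size back-solved on the assumption that 50 per group gives exactly 80 % under a two-sided t test. The article states neither the test nor the sidedness of the calculation, and if 50 had been rounded up, 48 might still suffice. The shortfall of two patients per group also arises only at the top of the range and only under n/(1 − d).
- A reader might infer that the attrition allowance has the wrong basis, because the section defines a dropout by the 3-month evaluation while the primary endpoint covers 7 days. The article does not say that the 15 to 20 % is loss for the 7-day endpoint. If it is 3-month loss, some of those patients would still have 7-day data, and the allowance would be cautious. That works against the power argument. No 7-day attrition figure is given from which to rebase it.

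**Conclusion.** The point stands as an internal arithmetic error and contradiction. The Statistics section states 120 per group (240 in total) where its own inputs give 59 to 63 per group (118 to 126 in total), so the per-group figure is about double what the derivation supports. The 120 total in the Abstract and the Discussion is consistent with those inputs.

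This rests on the stated 50 per group, the stated 15 to 20 % attrition, two groups and equal allocation. It needs no assumption about variance, test or effect size. The gap at 20 % attrition (48 against 50 per group) is minor and is not a second error. The sentence should be corrected because it is the only derivation of a number that decides when recruitment stops.

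**What to change.** In the Statistics section, replace "120 patients are needed in each group" with: 60 patients per group, 120 in total. Add that this keeps at least 50 evaluable patients per group for attrition up to about 16.7 %, and that 20 % attrition would leave 48 per group. The three statements of trial size then agree.

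No power figure needs restating, since the quantities behind the 50 per group are not given, and the article offers no basis for replacing the attrition allowance. The cost is one corrected sentence and a short addition, with no extra patients and no change to the enrolment given in the Abstract. If the sponsor did intend 240, the Abstract, the Discussion and the attrition step would all have to change instead, and nothing in the article points that way.

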### After 24 h, patients are randomly assigned between two groups of treatment:

Treatment group: 10 ml/h continuous infusion of ropivacaine 0.2 % + methylprednisolone 1 mg/kgPlacebo group: 10 ml/h continuous infusion of saline 0.9 %.

Regardless of treatment group, rescue analgesia in the first 48 h is provided by PCA pump with morphine (0.5 mg/ml, bolus 1 mg, lock-out 5 min, 20 mg limit every 4 h).

Random group allocation of patients is made through a computer-generated sequence. To maintain blinding, a research fellow who is not taking part in patient evaluation is in charge of preparing and programming all of the pumps used during the study: an opaque, sealed, sequentially numbered envelope is assigned to each patient and is opened by the same research fellow after the first 24 h of treatment.

Patients and their anesthesiologists are blind to treatment assignment. A clinical resident, who is not involved with randomization, is in charge of all clinical evaluations as part of the daily clinical practice.

The envelope is maintained apart from the patient’s case report form and is to be opened in every potentially harmful situation for the patient but only when care providers need to be aware of the patient’s treatment. All ropivacaine and methylprednisolone vials used during the study are registered with their code in order to be tracked and recognized in the future for any issue potentially hindering the validity of data.

At 48 h, morphine PCA is removed, and all patients are treated with Patient-Controlled Intrawound Analgesia (PCA through the wound catheter) with either ropivacaine 0.2 % alone or saline according to the group of randomization up to a maximum of 7 days after surgery. The catheter is removed at the seventh postoperative day or after 36 h of non-use (no self-administered bolus). After PCA removal, rescue additional analgesia is provided by tramadol (100 mg or 50 mg according to patient’s weight of not more than or of more than 50 kg).

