### Procedures - inflammatory response study

Inflammatory response will be analyzed on the first 15 patients in each group (for a total of 30 patients). Before the end of surgery, the surgeon inserts a single-use and minimally invasive (diameter of 0.5 mm) micro-dialysis catheter in the fat adjacent to the surgical wound with sterile technique. The catheter has a cutoff membrane (length of 30 mm) of 100,000 Da, which allows the monitoring of inflammation in vivo. The catheter’s characteristics allow extended use without risk of breaking. The catheter will be connected to a slow-rate infusion pump with imposition of 3 μl/min of micro-dialysis liquid, a high molecular weight (30 g dextran 60/1000 ml) substance to facilitate the micro-dialysis that remains inside the catheter. The dialyzed liquid is collected in dedicated tubes directly in the infusion pump. Sampling will be performed at 1, 6, 24, 48, and 72 h. Serum samples at the same time points are collected to compare systemic and local inflammations. All samples are stored at −80 °C until analysis. Concentrations of ILs (IL-1, IL-6, IL-8, and IL-10), interferon-gamma, and tumor necrosis factor-alpha are analyzed in dialyzed wound samples (local inflammation) and in serum (systemic inflammation). Cytokine levels in dialyzed liquid and in serum are tested by enzyme-linked immunosorbent assay (ELISA) by using a commercial kit.

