### Procedures - oxidative stress study

Oxidative stress will be analyzed on the first 15 patients in each group (for a total of 30 patients). Patients are sampled before surgery, before morphine bolus, and at 24 and 48 h after surgery.

Urine samples are directly aliquoted and stored at −80 °C; blood samples are collected in EDTA-containing vials and centrifuged within 30 min at 1000×*g* for 15 min at 4 °C to obtain the plasma.

Lipid peroxidation is analyzed through the determination of malondialdehyde with thiobarbituric acid assay in both plasma and urine. The 8-deoxyguanosine and poly(ADP-ribose) polymerase (PARP) are determined by commercial ELISA kits.

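### The biomarker analysis tests for arm differences at samples taken before the arms diverge at 24 h; treating those samples as a common baseline would use them better

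*Protocol article*

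**What the plan says.** The Methods give every patient the same ropivacaine and methylprednisolone infusion for the first day (Procedures - clinical study). Allocation comes next: "After 24 h, patients are randomly assigned between two groups of treatment". The sealed envelope "is opened by the same research fellow after the first 24 h of treatment".

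For cytokines, in wound dialysate and in serum, "Sampling will be performed at 1, 6, 24, 48, and 72 h". For oxidative stress, "Patients are sampled before surgery, before morphine bolus, and at 24 and 48 h after surgery".

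The Statistics section plans a repeated-measures regression "including time, group, and their interaction", and then: "Post-hoc comparisons will include within-group changes over time and between-group differences at each assessment". It says that P values will be adjusted for multiple testing and names no method for the biomarkers. It does not set the samples up to 24 h apart as baseline.

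On selection: "Inflammatory response will be analyzed on the first 15 patients in each group", 30 in total, with the same rule for oxidative stress. The surgeon places the micro-dialysis catheter before surgery ends.

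The Discussion gives the study of cytokines after the 24 h suspension of treatment as one reason for the design. The only early between-group check it mentions concerns morphine consumption at 24 h.

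**The concern.** Until 24 h the two groups differ in nothing but a label not yet revealed, so any biomarker difference between them at those times is chance. The substudy's question is what happens when the active infusion is stopped at 24 h in one arm and continued in the other. Only the 48 and 72 h cytokine samples, and the single 48 h oxidative-stress sample, can answer it.

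An analysis that allows a free arm effect at every time, and tests each one, gives the same standing to comparisons that cannot show a treatment effect. With 15 patients per arm there is little power to spare. The early samples also have a better use: they are repeated baseline measurements that can sharpen the later comparison.

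A smaller matter concerns selection. The catheter goes in about a day before the arm is known, so the arm sizes among the patients who receive one cannot be steered.

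**Working it through.** **Plan's own figure.** 15 × 2 = 30 patients. The article gives no effect size, SD or power for the substudy, so there is no power figure to reproduce.

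**Samples against allocation.**

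| Substudy | Times | Up to 24 h | After 24 h |
|---|---|---|---|
| Cytokines | 5 | 3 (1, 6, 24 h) | 2 (48, 72 h) |
| Oxidative stress | 4 | 3 (pre-surgery, pre-bolus, 24 h) | 1 (48 h) |

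The 24 h sample sits on the boundary. The article does not say whether it is drawn before the pump is changed, but it cannot reflect meaningful exposure to the allocated treatment.

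**Count of between-group contrasts, cytokines.** 6 analytes × 2 compartments × 5 times = 60. Of these, 6 × 2 × 3 = 36 are at or before 24 h and 6 × 2 × 2 = 24 are after it.

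**Dilution of a group main effect.** If the effect is d at every sample after 24 h and zero before, the equally weighted average over times is 2/5 = 0.40 d for cytokines and 1/4 = 0.25 d for oxidative stress.

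**Illustrative power.** Assumptions, none of them from the article: d = 0.8 SD, constant after 24 h; equal correlation ρ = 0.5 between any two times; n = 15 per arm; two-sided 5 %; one analyte, no multiplicity adjustment.

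*Group-by-time interaction*, with T times of which p are after 24 h and q up to 24 h. Noncentrality λ = (n/2) · d² · (pq/T) / (1 − ρ), chi-square on T − 1 df with the covariance treated as known.
- Cytokines: 7.5 × 0.64 × (6/5) / 0.5 = 11.52 on 4 df; power 78 %.
- Oxidative stress: 7.5 × 0.64 × (3/4) / 0.5 = 7.20 on 3 df; power 60 %.

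*Mean after 24 h, adjusted for the mean of the samples up to 24 h.* Residual variance = V(post) − ρ² / V(pre), where V(k samples) = (1 + (k − 1)ρ)/k. V(pre) = (1 + 2 × 0.5)/3 = 0.667 in both substudies.
- Cytokines: 0.75 − 0.25/0.667 = 0.375; SE = √(0.375 × 2/15) = 0.224; 0.8/0.224 = 3.58; power 93 % (noncentral t, 28 df).
- Oxidative stress: 1 − 0.25/0.667 = 0.625; SE = √(0.625 × 2/15) = 0.289; 0.8/0.289 = 2.77; power 76 %.

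*Sensitivity to ρ at d = 0.8 (interaction, then adjusted contrast).*

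| ρ | Cytokines | Oxidative stress |
|---|---|---|
| 0.3 | 62 %, 86 % | 45 %, 64 % |
| 0.5 | 78 %, 93 % | 60 %, 76 % |
| 0.7 | 96 %, 99 % | 84 %, 93 % |

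The order is the same throughout, but the gap narrows as ρ rises. At d = 1 and ρ = 0.5 the cytokine figures are 94 % and 99 %.

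**Split of the first 30.** Under simple 1:1 randomisation, which the article does not state, P(exactly 15/15) = C(30,15)/2³⁰ = 14.4 %. The number of consecutive patients N until both arms hold 15 has P(N = k) = 2 · C(k − 1, 14) / 2ᵏ for k ≥ 30. Its mean is 34.3, median 33 and 95th percentile 42. Complete balanced blocks would give 15/15 at about 30.

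**The case against.** The best defence is that the plan already contains the term it needs. The group-by-time interaction is the natural test for groups that start alike and then diverge, it is valid, and it keeps most of the power. Constraining the early means is a gain in efficiency, and such detail is often left to an analysis plan, which is not shown here. This largely stands. What remains is that the article itself commits to between-group tests at every assessment without exempting the early ones.

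Several stronger readings are tempting, and the article does not support them:

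- *The authors overlooked the 24 h switch.* The Discussion gives it as a reason for the design. Only the stated analysis fails to use it.
- *Most of the information is wasted.* That would follow if the group main effect were the test of interest; its power under the same assumptions is 19 % (cytokines) and 10 % (oxidative stress). The Statistics section does not name it as such.
- *The cytokine threshold is 0.05/60.* Bonferroni is named only for candidate genes, and no biomarker family is defined. The count of 60 contrasts is arithmetic, not the plan's multiplicity family.
- *Chance early differences will pass as treatment effects.* The post-hoc tests are time-specific and adjusted, so a difference at 1 or 6 h would be recognisable as preceding allocation.
- *Fifteen per group is impossible.* The rule governs who is analysed. It can be met by sampling consecutive patients until both arms reach 15. The 14 % and 34-patient figures hold only under simple randomisation; the article mentions just a computer-generated sequence and may have omitted blocking. The catheter argument also does not reach the oxidative-stress substudy, which uses blood and urine.

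The early samples also serve other stated aims, such as within-group time courses and the comparison of local with systemic inflammation. They should be kept.

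**Conclusion.** The point holds as a matter of efficiency and clarity in a secondary, mechanistic substudy; the primary endpoint is untouched. That three of five cytokine times and three of four oxidative-stress times cannot carry an arm effect follows from the schedule alone. The dilution of a group main effect to 40 % or 25 % further needs a constant effect after 24 h and equal weighting of times.

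The power loss of about 15 percentage points (78 to 93 %) for cytokines and 16 (60 to 76 %) for oxidative stress is illustrative. It rests on the assumed 0.8 SD effect, equal correlation of 0.5 and 15 per arm, and the adjusted cytokine contrast benefits from assuming the same effect at 48 and 72 h. The loss matters most for oxidative stress, which has a single informative sample.

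The selection rule is imprecise rather than unworkable. How many catheters it takes to fill both arms depends on a randomisation scheme that the article does not describe.

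**What to change.** Use a repeated-measures model with one common mean for both arms at every sample up to and including 24 h, and arm effects only at 48 and 72 h for cytokines and at 48 h for oxidative stress. Adjusting the later values for the samples up to 24 h is an acceptable alternative. Limit the between-group tests and the multiplicity count to those later times, and keep the earlier samples for within-group time courses.

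Define the substudy as the first 30 consecutive randomised patients, with whatever split results. The Trial status section reports 46 patients enrolled, so substudy recruitment may already be complete; in that case report the actual split.

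The cost is a few sentences in the analysis plan and one on selection, with no new data. A mildly unequal split costs little: 12/18 keeps 4 × 12 × 18 / 30² = 96 % of the efficiency of 15/15.
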